## Secondary outcome measures - tolerability

A secondary clinical outcome measure will be the tolerability of artesunate compared with placebo. Tolerability will be assessed according to conventional criteria used in clinical trials, and scored on standardised pro-formas.

Comparisons will also be made between baseline haematological and biochemical variables (FBC, LFT, urea and electrolytes), and these measures repeated once treatment stops and before surgery.

## Other histological assessments

These will be detailed assessments including those of tumour markers and other surface markers in routine use at St. George’s. Biopsies will be assessed specifically for specialised assays, carried out in [name] laboratory (Heidelberg) and will include:

- Determination of apoptosis using TUNEL assay (using a commercially available kits) – this is the primary endpoint of this study
- Immunohistochemical analyses of paraffin-embedded tumor sections with particular assessment of vascular endothelial growth factor (VEGF), *c-myc* status and EGF-receptor status
- Determination of microvessel density
- Proliferative activity (Ki-67 staining)

Material will be obtained at the time of resection of the tumour for routine histological purposes, and surplus material will be used for the histological studies listed. Several small pieces of tumour material (1 mm3) will also be collected into RNA later™ (Trizol), or without preservative and stored at

-70°C or below for expression studies using microarrays, and other genomic analyses.

An aliquot of serum will be stored on admission and just before surgery, for proteomic analyses (carried out at St. George’s). **PBMC typing, and the effect of artesunate on expression of cell surface markers will be assessed.**

## Interim analysis

An interim analysis comprising efficacy and tolerability criteria will be performed once the first ten patients have completed the study.

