# Study Design

This will be a Phase I randomised placebo-controlled double-blind trial of artesunate given orally to patients with histologically confirmed CRC who will receive treatment with curative intent. The study will involve 22 patients randomly assigned to receive artesunate or placebo. The overall study duration will be 14 days. An interim efficacy analysis is planned after the first ten patients have completed the study.

A Data Monitoring Committee (DMC) will supervise the study. The primary role of the DMC is to protect the safety of the patients participating in the study by reviewing the safety information. Clear criteria for terminating the study prematurely are given. The DMC is composed of three individuals, an individual with expertise in the conduct of drug trials involving artesunate, a statistician and a colorectal surgeon with a specialist knowledge of the management of colorectal cancer.

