## List of criteria for premature discontinuation of the study

The study may be discontinued prematurely by the Sponsor, the DMC or the Principal Investigator if:

- As a result of the interim analysis or any other event during the study there is doubt as to the risk/benefit ratio
- The results of the trial do not appear to be scientifically convincing to the Sponsor
- The aim of the study has become outdated or is no longer of interest
- There is a breach by the investigator of a fundamental obligation under this agreement, including but not limited to breach of the Study Protocol, breach of the applicable laws and regulations or breach of the ICH guidelines for Good Clinical Practice

In all cases the LREC, MHRA and Health Authority will be informed.

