# Outcome Measures

## Primary outcome measure - efficacy

The primary outcome measure for the treatment response study will be a significant difference in the proportion of cells that exhibit apoptosis between the 2 treatment groups (placebo and artesunate). As CRC is unlikely to exhibit significant apoptosis if untreated, >7% of cells with apoptotic features will be considered significant and consistent with drug effect. As there will be placebo-controlled subjects in this study (who will receive the conventional pre-operative standard of care), the proportion of subjects who have increased proportion of apoptotic cells in artesunate recipients will be compared with those receiving placebo.

The following sample size has been estimated by the statistician using Clinistat:

Estimated sample size for two-sample comparison of proportions

Test Ho: p1 = p2, where p1 is the proportion in population 1

and p2 is the proportion in population 2

Assumptions:

alpha = 0.0500 (two-sided)

power = 0.9000

p1 = 0.0500 (i.e. 1 patient or none will have apoptotic cells in placebo recipients).

p2 = 0.58 (i.e. 7 patients will have apoptotic cells in artesunate recipients).

n2/n1 = 1.00

Estimated required sample sizes:

n1 = 11

n2 = 11

This sample size has the power to detect a difference between apoptosis rates of 18% and 75%. This outcome measure will be scored without knowledge of intervention, as this is a double-blind investigation.

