## Statistics

All analyses will be made on an intention to treat basis. Statistical significance will be assumed at a 5% level.

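### The planned efficacy analysis at 10 of 22 patients has no alpha allocation, boundary or bar on an interim claim, so the 5% error rate is not assured

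*Combined protocol and SAP*

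**What the plan says.** Study Design: "An interim efficacy analysis is planned after the first ten patients have completed the study". The Interim analysis section repeats this in its only sentence: "An interim analysis comprising efficacy and tolerability criteria will be performed once the first ten patients have completed the study".

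The Statistics section asks for intention-to-treat analysis throughout and then gives the only significance rule in the plan: "Statistical significance will be assumed at a 5% level". It does not say which look this applies to.

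The premature-discontinuation list gives one reason that mentions the interim: "As a result of the interim analysis or any other event during the study there is doubt as to the risk/benefit ratio". The other reasons are results that do not convince the sponsor, an aim that is outdated or no longer of interest, and a breach by the investigator. All are qualitative, and none is a rule for stopping because efficacy has been shown.

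The primary outcome section describes the endpoint in two ways: as the proportion of cells showing apoptosis, and as the proportion of subjects with increased apoptosis. The test is described only by the sample-size line "Estimated sample size for two-sample comparison of proportions", which does not say whether a continuity correction or an exact test is meant.

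**The concern.** Study Design calls the interim an efficacy analysis, and the plan gives one significance level for everything. If a p-value below 0.05 counts at ten patients and again at 22, a false-positive result has two chances to occur, and the overall error can exceed the 5% on which the trial was sized. The risk falls on the primary claim. An early positive result would also rest on about five patients per arm, where an estimate that has just crossed a significance threshold tends to overstate the effect.

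**Working it through.** **Inputs.** From the primary outcome section: two-sided alpha 0.05, power 0.90, responder rates 0.05 (placebo) and 0.58 (artesunate), 11 per arm. From Study Design: 22 patients, interim after 10. From Treatment group assignation: equal allocation. Assumption: the interim splits 5 v 5, because the protocol does not say how the allocation is balanced.

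**The plan's own figure.** The unpooled formula gives n = (1.960 + 1.282)² × [0.05 × 0.95 + 0.58 × 0.42] / 0.53² = 10.89, so 11 per arm, as stated. The pooled formula gives 14, and 18 with continuity correction. The planning figure therefore does not point to Fisher's test or a corrected test.

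**Continuous endpoint, 5% at both looks.** The information fraction is 10/22 = 0.4545, so the two test statistics have correlation √0.4545 = 0.674. Then 1 − P(|Z1| < 1.96, |Z2| < 1.96) = 0.0846. Of this, 4.23% favours artesunate, against 2.5% for a single look. A simulated t-test (400,000 runs) gives 8.6%.

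**Responder endpoint, 5% at both looks.** All tables for 5 v 5 and then 11 v 11 were enumerated under a common rate. For the uncorrected (pooled) two-proportion test:

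| Common rate | Interim alone | Final alone | Either look |
|---|---|---|---|
| 5% (planned placebo rate) | 0.2% | 0.2% | 0.3% |
| 10% | 1.0% | 1.2% | 1.9% |
| 18% | 3.3% | 3.1% | 5.5% |
| 30% | 5.8% | 4.3% | 8.65% |
| 50% (maximum) | 6.05% | 5.28% | 9.69% |

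The 18% row is included because the primary outcome section also mentions a comparison of 18% with 75%. The interim entry at 50% can be checked by hand. The test rejects for 0 v 3, 0 v 4, 0 v 5, 1 v 5 and 2 v 5 and their mirror images, which gives 2 × (10 + 5 + 1 + 5 + 10)/1024 = 0.0605. Other interim splits give maxima of 8.9% (4 v 6) and 9.9% (3 v 7).

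Maximum two-look error for the other tests, 5 v 5 then 11 v 11:

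- Fisher's exact test: 3.4%.
- Continuity-corrected test: 1.9%.
- Unpooled test: 14.0%. Much of this is the test's own small-sample error, since the final look alone gives 9.1% at a 20% common rate. It should not be charged to the interim.

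**Chance of p ≤ 0.05 at the interim if the planned rates are true.** Placebo: P(0 of 5) = 0.95⁵ = 0.774, P(1) = 0.204, P(2) = 0.021. Artesunate: P(3) = 0.344, P(4) = 0.238, P(5) = 0.066.

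- Fisher rejects for 0 v 4, 0 v 5 and 1 v 5: 0.774 × (0.238 + 0.066) + 0.204 × 0.066 = 0.25.
- The uncorrected test also rejects for 0 v 3 and 2 v 5: 0.25 + 0.774 × 0.344 + 0.021 × 0.066 = 0.52.

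**A boundary, if one is wanted.** The O'Brien-Fleming-type spend for a two-sided 5% design is 4[1 − Φ(2.2414/0.674)] = 4[1 − Φ(3.325)] = 0.0018 at 10/22. The smallest possible p at 5 v 5 (0 v 5) is 2/252 = 0.0079 for Fisher. For the uncorrected test, z = 1/√(0.25 × 0.4) = 3.16, so p = 0.0016.

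**The case against.** The strongest reply is that inflation needs an efficacy claim to be possible at the interim, and no section says that it is. The listed reasons for stopping concern doubt about risk and benefit, unconvincing or outdated work, and breach. Stopping only for such reasons does not raise the false-positive rate. This stands: a reader might infer that the trial's error rate simply is 8.5%, and the documents do not support that. The risk/benefit criterion should not be read as an efficacy stop either.

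The second reply is that the size depends on a test the plan does not name. This also stands. With Fisher's test or the continuity correction, two unadjusted looks stay below 5%. With the uncorrected test, the 9.7% belongs to a 50% rate in both arms, far from the assumed 5% placebo rate, where the error is 0.3%.

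Neither reply closes the gap. Silence on an interim claim does not prevent one, particularly when Study Design calls the look an efficacy analysis. A conservative test cannot be relied on unless it is specified, and at 11 v 11 Fisher's test has about 68% power for 5% v 58%, not the 90% planned. The 5% placebo rate is an assumption, whereas error control should hold whatever the common rate is.

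A reader might also infer that the look is useless for efficacy because a strict boundary could never be crossed. That is true of Fisher's test at 5 v 5 (0.0079 against 0.0018), but not of the uncorrected test (0.0016).

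**Conclusion.** The point holds in conditional form. The plan schedules an efficacy analysis after 10 of 22 patients, under a single 5% level, with no alpha allocation, boundary or bar on an interim claim, so control of the 5% error is not assured. If efficacy may be claimed at 5% at either look, the overall error is about 8.5% on the cell-proportion reading. On the responder reading with the uncorrected test it is at most 9.7%, falling to 5.5% at an 18% common rate and 0.3% at 5%. It stays under 5% with Fisher's test or the continuity correction. The responder figures assume a 5 v 5 interim. The documents show an unspecified rule that permits inflation, not a demonstrated breach of the 5% level.

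**What to change.** Replace the Interim analysis section with text such as:

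> The interim review after ten patients is for safety and tolerability, with optional non-binding futility, and is conducted by the Data Monitoring Committee. The trial will not stop for efficacy and no efficacy claim will be made at the interim. The single final primary analysis is tested at two-sided 5% using [named test].

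Bring the Study Design sentence into line with this. Naming the test also means settling whether the primary endpoint is the proportion of cells or the proportion of responders. If the uncorrected test is chosen, note that its final look alone reaches 5.28% at worst.

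If an efficacy stop is wanted, pre-specify the boundary and its alpha allocation, for example two-sided O'Brien-Fleming-type spending of about 0.0018 at 10/22, with the final level adjusted to match. Check that the named test can reach that boundary at the interim size, and confirm the overall error by enumeration.

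The cost is one paragraph and no extra patients. What is given up is an early efficacy stop on about 5 v 5 patients, which at 5% v 58% has about a 25% chance with Fisher's test and 52% with the uncorrected test. Safety oversight by the committee is unchanged.

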## Blinding

All assessments of primary or secondary endpoints will be undertaken by investigators blinded to treatment group.

## Statistics

All analyses will be made on an intention to treat basis. Statistical significance will be assumed at a 5% level.

# Ethical and regulatory standards

This study will be conducted in accordance with the principles laid down in the Declaration of Helsinki, and the International Conference on Harmonisation guidelines for Good Clinical Practice. Access to the data will be according to the Data Protection Act.

All patients will be fully informed by the investigators of all pertinent information to the trial in language and terms that they are able to understand. A written Patient Information Sheet (Appendix 3), approved by the Wandsworth LREC and the Sponsor will be provided as will an opportunity to ask questions of the investigators. Participation in the trial will not occur until a standard, approved Informed Consent Form has been signed and dated.

Approval for the study is being sought from the Wandsworth LREC of the National Research Ethics Service, the St George’s Healthcare NHS Trust Research and Development Office and the MHRA.

The relevant regulatory authorities including the DMC will have full access to all study documentation at all times.

# Miscellaneous Considerations

## Financing and Insurance

Artesunate and placebo are being provided free of charge by Dafra Pharma. The study is funded from [name] and [name] Funds.

## Insurance Compensation

Indemnity will be provided through the schemes operated by St George’s, University of London according to standard agreements.

## Publication Policy

Investigators agree not to make any publication, communication or release pertaining to the results of the study without the prior written permission of the Principal Investigator.

# Appendix 1: Study design

Randomisation

Artesunate 200mg od for 14 days

Placebo for 14 days

**Referral, diagnosis, surgery planned**

Day 0

Day7

Day14

Recruitment interview and randomisation

<62 days

Midpoint assessment

End of treatment assessment

**Surgery**

(post-treatment review)

# Appendix 2: Sample Case Record Form

#

#
[figure not shown]

#
[figure not shown]

#
[figure not shown]

#
[figure not shown]

#
[figure not shown]

#
[figure not shown]

#
[figure not shown]

#
[figure not shown]

#
[figure not shown]
